**Fig. 2 Fig2:**
[figure not shown]
Schedule of the follow-up moments and associated assessments and investigations. (1) Follow-up specific for patients receiving neo-adjuvant chemotherapy. (2) Follow-up specific for patients in treatment arm 2. (3) At predefined follow-up visits a standard blood control (including erythrocytes, leucocytes (including formula), thrombocytes, sedimentation, creatinine, electrolytes, liver/renal and inflammatory parameters) is performed. Abbreviations: QOL: quality of life; CT: computed tomography; MRI: magnetic resonance imaging; ^18^F-FDG-PET-CT: ^18^F-fluorodeoxyglucose-positron emission tomography-computed tomography; RC: radical cystectomy; TMT: trimodality treatment; MDT: metastasis-directed therapy; M: month(s); FU: follow-up

### Data management and confidentiality

All study data will be handled in accordance with the law on General Data Protection Regulation (GDPR) and institutional rules. The collection and processing of personal data from subjects enrolled in this study will be limited to those data that are necessary to fulfill the objectives of the study. Study-related data of the patient will be provided in a coded manner to Ghent University Hospital. A sequential unique and coded study ID number will be attributed to each patient included into the trial, to maintain participants confidentiality. Identification of patients must be guaranteed at the center of inclusion. In order to avoid identification errors, the year of birth and the unique Study ID Number need to be provided on the case report form. All data will be collected and managed using REDCap (Research Electronic Data Capture) electronic data capture tools hosted at Ghent University Hospital, a secure web-based application designed to support data capture for research studies [18]. Patient data will be stored for 25 years.

### Statistical analyse

#### Sample size

This is a multicentric prospective phase II study in which 156 patients will be enrolled. A confidence interval for the 2-year OS was estimated using the Kaplan Meier survival estimates and corresponding confidence intervals (type ‘log-log’). These Kaplan Meier survival estimates are based on binomial proportions. When the true proportion of survival is 63% for arm 2 + 3, a sample size of 35 patients (39 when taking into account 10% drop-out rate) in group 2 + 3 yields 80% power to show that the proportions of patients surviving at 2 years, is 38% or more using an exact binomial test at alpha level 5% [12]. We expect 1/4 patients to have a positive ^18^F-FDG-PET-CT, based on the unpublished observations of [name] et al.

#### Subsequent analyses

Descriptive statistics will be used to summarize patient characteristics and toxicity per treatment group. Progression and survival are defined as mentioned above and calculated from time of diagnosis to disease progression or death. Survival analysis will be compared between groups using the log-rank test. Kaplan-Meier estimates of 2-year PFS, DMFS, DSS and OS will be provided for each treatment group and as a post-hoc subgroup analysis based on patient characteristics described above. Median follow-up time will be derived using both complete and incomplete follow-up times. Cox proportional hazards regression will be used to provide hazard ratio estimates. A *p*-value of less than 0.05 will be considered statistically significant. For the evaluation of biomarkers on one time point, differences between groups will be tested using the Mann-Whitney U test. For the evaluation of biomarkers over time, differences between groups will be tested using the Wilcoxon signed-rank test. To evaluate correlations, Spearman correlation coefficients will be calculated. A p-value of less than 0.05 will be considered statistically significant.

All statistical analyses will be performed using SPSS (SPSS Inc., Chicago, Il, USA).

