### Objectives

The primary endpoint is the 2-year overall survival (OS) rate defined as the percentage of patients alive at 2 years after diagnosis of MIBC. OS is calculated from time of diagnosis until death due to MIBC or other causes.

Secondary endpoints are progression-free survival (PFS, defined as time of diagnosis until progression: i.e. local (T2-T4 in case of of TMT)/locoregional recurrence or extra-pelvic metastases), distant metastasis-free survival (DMFS, defined as time of diagnosis until occurrence of distant metastasis on repeated imaging), disease-specific survival (DSS, defined as time of diagnosis until death due to MIBC) and quality of life (QOL) evaluated by the general EORTC QOL questionnaire QLQ-C30 (version 3) and the bladder cancer specific module QLQ-BLM30. The added diagnostic value of ^18^F-FDG-PET-CT compared to conventional imaging will be evaluated. If neo-adjuvant chemotherapy is administered, the treatment response will be evaluated on the repeated ^18^F-FDG-PET-CT. A biopsy specimen of the bladder, obtained after transurethral resection of the bladder (TURb) as well as urine and blood samples will be collected for validation of predictive biomarkers by evaluating the correlation between response to therapy and outcome (PFS, DMFS, DSS and OS) with in literature reported biomarkers determined on biopsy specimen of the bladder, obtained after TURb.

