### Intervention

#### Imaging

Conventional imaging, consisting of standard thoracic CT and abdominopelvic CT (or MRI), will be performed prior to the radical local therapy. In case of neo-adjuvant chemotherapy, conventional imaging will be performed prior to and after neo-adjuvant chemotherapy. After the second cycle of chemotherapy, MRI bladder will be performed to evaluate provisional therapy response. In addition to and at timing of the conventional imaging patients will receive an ^18^F-FDG-PET-CT. We aim to perform the ^18^F-FDG-PET-CT within 1 month of the thoracic CT and abdominopelvic CT (or MRI).

The ^18^F-FDG-PET-CT procedure is described in detail in an additional file (see Additional file 2).

Conventional imaging images will be evaluated by experienced radiologists in uro-oncology. ^18^F-FDG-PET-CT images will be reviewed and analyzed by a nuclear medicine physician and a radiologist experienced in reading PET-CT images. Evaluation of the ^18^F-FDG-PET-CT images will occur blinded to the conventional imaging or vice versa in case the ^18^F-FDG-PET-CT is performed first.

After ruling out presence of distant metastases on conventional imaging and evaluation of the ^18^F-FDG-PET-CT’s, patients will be allocated to the appropriate treatment arm:
Arm 1: ^18^F-FDG-PET-CT ➜ T1–4 N0–3 M0Arm 2: ^18^F-FDG-PET-CT ➜ T1–4 N0–3 M1 (≤3 metastases)Arm 3: ^18^F-FDG-PET-CT ➜ T1–4 N0–3 M1 (> 3 metastases)

If no neo-adjuvant chemotherapy is administered, group allocation is based on the findings of the single ^18^F-FDG-PET-CT. In case of neo-adjuvant chemotherapy, group allocation is based on ^18^F-FDG-PET-CT with the highest number of distant metastases. Thus, patients who show a decrease of the total number of metastases or a complete response on the second ^18^F-FDG-PET-CT, will be allocated based on the result of their first ^18^F-FDG-PET-CT.

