#### Treatment

All included patients will receive a standard of care approach which involves either RC with extended pelvic lymph node dissection (ePLND) or TMT consisting of a visible complete TURb and radiochemotherapy. Radiochemotherapy consists of moderately hypofractionated radiotherapy to a dose of 55 Gy in 20 fractions to the bladder, in combination with a radiosensitizer. In case of clinically node-positive disease, the pelvic nodal areas are included in the radiotherapy field. Decision of local therapy is at the discretion of the patient unless there is a contraindication for one treatment option. If the patient is eligible, neo-adjuvant chemotherapy will be administered.

^18^F-FDG-PET-CT information concerning the pelvic lymph nodes will be used to guide local treatment i.e. adapting the ePLND template or radiotherapy field, if feasible.

According to the risk-group allocation, treatment will be intensified by adding MDT or immunotherapy, in treatment arm 2 or 3, respectively. Patients will not be randomized. Both surgery and stereotactic body radiation therapy (SBRT) can be applied as MDT for oligometastases. The SBRT procedure is described in detail in an additional file (see Additional file 3). In treatment arm 3, systemic immunotherapy will be initiated in case of ^18^F-FDG-PET-CT detected polymetastatic disease. The systemic immunotherapy protocol can be adjusted following changes in guidelines and/or reimbursement criteria.

In case of diagnosis of metastases on the conventional imaging before local treatment is started, the patient is excluded from the trial and metastatic bladder cancer standard of care is initiated.

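### The sentence on biomarkers over time names a paired test (Wilcoxon signed-rank) for a difference between groups, which that test cannot assess

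*Protocol article*

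**What the plan says.** Two consecutive sentences under Subsequent analyses in the Protocol article deal with biomarkers. For a single time point: "For the evaluation of biomarkers on one time point, differences between groups will be tested using the Mann-Whitney U test". For repeated measurements: "For the evaluation of biomarkers over time, differences between groups will be tested using the Wilcoxon signed-rank test". The next sentences add Spearman coefficients and a 0.05 threshold: "To evaluate correlations, Spearman correlation coefficients will be calculated. A p-value of less than 0.05 will be considered statistically significant".

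The biomarker aim, under Objectives, is "validation of predictive biomarkers by evaluating the correlation between response to therapy and outcome (PFS, DMFS, DSS and OS"), using biopsy, urine and blood samples. The article does not define which groups the biomarker tests compare.

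The treatment groups are separate sets of patients. Under Imaging, after the scans are read, "patients will be allocated to the appropriate treatment arm"; under Treatment, "Patients will not be randomized". No matching of patients across groups is described.

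**The concern.** The signed-rank test works on one difference per pair. With repeated biomarker values the natural pair is the same patient at two times, so the test shows whether values moved. It has no term for group membership. Patients in different groups form no pairs, so the test cannot be applied across groups.

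An analyst who followed the sentence literally would have three courses: find that the test cannot be run, pool all patients and report a time effect as though it were a group effect, or test each group separately and compare the p-values. The last two can produce a claimed group difference where there is none, and pooling can also miss a real one. The results are to be judged at p < 0.05, so a false biomarker claim is possible.

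**Working it through.** **1. Reading the text.** The two biomarker sentences describe their target in identical words, as differences between groups. In the first, the test is Mann-Whitney, so the groups must be independent. Elsewhere in the section, survival is compared between groups and estimates are given per treatment group. Read consistently, the second sentence asks whether groups of patients differ in how a biomarker changes. The methods named for biomarkers are Mann-Whitney (one time point), signed-rank (over time) and Spearman (correlation). None is assigned to a group difference in change in a way that can test it.

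**2. Group sizes for an illustration.** The article gives no figure for the biomarker analysis. Under Sample size it gives 35 patients for arms 2 + 3 and 39 with 10% drop-out, "We expect 1/4 patients to have a positive ^18^F-FDG-PET-CT", and "This is a multicentric prospective phase II study in which 156 patients will be enrolled". These agree: 35 / 0.9 = 38.9, rounded up to 39; 39 × 4 = 156; 156 − 39 = 117 in arm 1. Using 117 and 39 as the biomarker groups, with complete pairs in all patients, is an assumption. So are the normal distribution and the effect sizes below.

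**3. Pooled use of the test** (4,000 simulated trials; SD 1 at each time, within-patient correlation 0.5).

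| True change, 117 patients / 39 patients | Signed-rank on all changes rejects | Mann-Whitney on changes by group rejects |
|---|---|---|
| +0.5 / +0.5 SD (no group difference) | 100% | 4.6% |
| −0.2 / +0.6 SD (real group difference) | 3.6% | 98.5% |

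In the second row the average change is (117 × (−0.2) + 39 × 0.6) / 156 = (−23.4 + 23.4) / 156 = 0. The signed-rank test responds to the average change and does not detect the group contrast.

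**4. Separate use in each group** (2,000 simulated trials; the same true change of 0.3 SD in both groups). The test is significant in 87.6% of trials with 117 patients and in 43.1% with 39. If the groups are independent, exactly one is significant with probability

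0.876 × (1 − 0.431) + (1 − 0.876) × 0.431 = 0.498 + 0.053 = 0.55.

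The simulation gave 55.9%. At other common changes the share was 52.6% (0.2 SD), 33.9% (0.4 SD) and 15.9% (0.5 SD). Mann-Whitney on the same changes rejected in 4.4% to 5.5% of trials.

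**The case against.** The best defence is that the two sentences contrast one time point with several, and pair them with an independent-samples test and a paired test. That is the textbook pairing if groups in the second sentence means sets of measurements at two times. This reading is plausible and makes the signed-rank test valid. The sentence would still be misworded, and the article would name no test of whether change differs between groups of patients.

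A reader might also infer stronger points that the documents do not support:

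- **That Mann-Whitney is wrong at single time points because there are three arms.** The biomarker groups are never defined as the three arms. The objective speaks of response and outcome, which suits two-group splits, and Sample size pools arms 2 + 3. Mann-Whitney is valid for two groups, and nothing in that sentence is stated wrongly.
- **That the plan has a false-positive rate of 34% to 56%.** Those figures belong to a rule that declares a difference when exactly one group is significant. The article states no such rule, and the range omits the 16% at 0.5 SD.
- **That unequal group sizes are the main cause of disagreement.** With two equal groups of 78, reruns still gave disagreement of 47% to 49% at 0.2 SD and 37% to 38% at 0.3 SD, against 52% to 53% and 55% to 56% with 117 and 39. At these effects much of the disagreement is ordinary limited power.

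The allowance for detail left to a fuller document does not remove the point, because the article names a specific test for a specific question and the two do not fit.

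**Conclusion.** The point holds as a minor one. As written, the sentence assigns a paired test to a between-group question, and nothing elsewhere in the article corrects it. This follows from the definition of the test and does not depend on any simulation setting. Whether the underlying error is in the method or only in the wording cannot be decided from the article.

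The reach is limited. The primary endpoint, the survival analyses and the sample size are unaffected. The article ties the biomarkers it describes to the bladder biopsy, so analysis over time probably concerns mainly blood and urine.

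**What to change.** State which question is meant, and write one sentence for each:

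- **Within-patient change:** the Wilcoxon signed-rank test, for change between two named time points in the same patients.
- **Difference between groups in change:** the Mann-Whitney U test on the within-patient changes for two groups, or Kruskal-Wallis for three or more, with the groups named.

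A model with a group-by-time term is an option, not a requirement. The groups are not randomised and may start at different biomarker levels, so change-score and baseline-adjusted analyses can answer different questions. The choice should be made before the data are examined.

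The cost is one or two sentences, with the same data and software and no change in the number of patients.

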**Methods:**

EFFORT-MIBC is a multicentric prospective phase II trial aiming to include 156 patients. Eligible patients are patients with histopathology-proven MIBC or ≥ T3 on conventional imaging treated with MIBC radical treatment, without extra-pelvic metastases on conventional imaging (thoracic CT and abdominopelvic CT/ magnetic resonance imaging (MRI)). All patients will undergo radical local therapy and if eligible neo-adjuvant chemotherapy. An ^18^F-FDG-PET-CT will be performed in addition to and at the timing of the conventional imaging. In case of presence of extra-pelvic metastasis on ^18^F-FDG-PET-CT, appropriate intensification of treatment with metastasis-directed therapy (MDT) (in case of ≤3 metastases) or systemic immunotherapy (> 3 metastases) will be provided. The primary outcome is the 2-year overall survival rate. Secondary endpoints are progression-free survival, distant metastasis-free survival, disease-specific survival and quality of life. Furthermore, the added diagnostic value of ^18^F-FDG-PET-CT compared to conventional imaging will be evaluated and biomarkers in tumor specimen, urine and blood will be correlated with primary and secondary endpoints.

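### Spearman is the only correlation method named for a biomarker objective that includes OS, PFS, DMFS and DSS; applied to these it ignores censoring and dilutes the association by roughly 20–30%

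*Protocol article*

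**What the plan says.** The biomarker objective appears twice in the protocol article. The abstract (Methods) states that "biomarkers in tumor specimen, urine and blood will be correlated with primary and secondary endpoints". The Objectives section describes the validation as done "by evaluating the correlation between response to therapy and outcome (PFS, DMFS, DSS and OS) with in literature reported biomarkers". The same section defines these outcomes as times from diagnosis; for the primary one, "OS is calculated from time of diagnosis until death due to MIBC or other causes".

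Subsequent analyses gives three sentences that bear on biomarkers. The first assigns the Mann-Whitney U test to markers measured once, and the second assigns the Wilcoxon signed-rank test to markers measured repeatedly. The third is the one at issue here: "To evaluate correlations, Spearman correlation coefficients will be calculated".

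Earlier in the same section, in general terms and without mention of biomarkers: "Cox proportional hazards regression will be used to provide hazard ratio estimates". That section also refers to incomplete follow-up times. Follow up and data collection ends survival follow-up at death, withdrawal of consent or the end of the study.

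**The concern.** Spearman's coefficient takes one number per patient and has no place for an event indicator. If that number is the recorded time to death or last contact, a patient censored at 2.5 years counts as a worse outcome than one who died at 3 years, although the first may live longer. The ranks then reflect partly survival and partly when the patient was enrolled or lost.

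Censoring will be common. The Background expects about 60% alive at 2 years and 50% at 5 years. For DSS, deaths from other causes are also not events. Neither of the two other tests named for biomarkers handles censoring.

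At stake is the biomarker result: a real association would be reported as weaker than it is, and some would be missed. The coefficient would also depend on the length of follow-up at the data cut-off, so it could not be compared with other reports.

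**Working it through.** **The plan's own figures.** No sample size or power is stated for the biomarker analysis. The numbers of patients come from the primary endpoint and reproduce. With an exact binomial test of 38% against 63%, n = 35 and an upper tail of 0.025, success needs at least 20 survivors, the actual tail is 0.0167 and the power is 81.5%. Then 35 / 0.9 = 38.9, rounded to 39, and 39 × 4 = 156.

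**Inputs from the document.** N = 156 in total, 39 in arms 2 + 3, 10% drop-out (Sample size); about 60% alive at 2 years (Background).

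**Assumed inputs.** A standard normal biomarker x; hazard ratio (HR) per SD of 1.0, 1.5 or 2.0; exponential survival; the censoring patterns in the table.

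**Formulas.** Baseline hazard λ = -ln(0.60)/2 = 0.255 per year. Survival time T is exponential with hazard λ·HR^x. Observed time Y = min(T, C), where C is the censoring time. Compare Spearman(x, T), which could be had only with complete follow-up, with Spearman(x, Y), which the data would give. Loss = 1 - Spearman(x, Y)/Spearman(x, T). Each row is the mean of 500 simulated trials, or 2,000 for the drop-out rows.

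| n | HR per SD | Censoring | Censored | Spearman, complete | Spearman, observed | Loss | Power, Spearman / Cox |
|---|---|---|---|---|---|---|---|
| 156 | 1.5 | all at 2 years | 59% | -0.320 | -0.245 | 23% | 87% / 90% |
| 156 | 1.5 | 2–5 years | 42% | -0.319 | -0.255 | 20% | 89% / 96% |
| 156 | 1.5 | 2–5 years, 10% lost in years 0–2 | 45% | -0.319 | -0.229 | 28% | 83% / not run |
| 156 | 1.5 | 0–5 years | 56% | -0.323 | -0.172 | 47% | 57% / 92% |
| 156 | 2.0 | 2–5 years | 42% | -0.495 | -0.408 | 18% | 100% / 100% |
| 156 | 2.0 | 2–5 years, 10% lost in years 0–2 | 45% | -0.491 | -0.370 | 25% | 100% / not run |
| 39 | 2.0 | 2–5 years | 41% | -0.483 | -0.399 | 17% | 73% / 85% |
| 39 | 2.0 | 0–5 years | 55% | -0.481 | -0.267 | 44% | 39% / 72% |

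Example of the loss, third row: 1 - 0.229/0.319 = 0.28.

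**False positives.** With HR 1.0 and censoring unrelated to the biomarker, Spearman rejects in 3–6% of trials at the 5% level. The rate rises only if the biomarker is tied to length of follow-up. With 60% alive at 2 years, follow-up of 2–5 years, n = 156 and no true effect, an assumed correlation between biomarker and follow-up length of 0.1 gives about 6%, 0.2 about 10% and 0.37 about 21%. In an extreme case (correlation about 0.8), Spearman rejects in 99% of trials with a spurious coefficient of +0.36, while Cox rejects in 8% with a mean log hazard ratio of 0.003.

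**Limit of the model.** A constant hazard gives 0.60^(5/2) = 28% alive at 5 years, below the 50% in the Background. Fewer late deaths would leave more times censored than the 2–5 year rows show.

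**The case against.** The Spearman sentence names no endpoint, so the link to OS, PFS, DMFS and DSS is read across sections. The article uses the word correlated loosely elsewhere: the Background and Discussion call the PET result correlated with survival where a comparison between groups is meant. Spearman also has sound uses here: marker against marker, QOL scores (which are among the secondary endpoints) and response to therapy. The primary endpoint is a percentage alive at 2 years, and the Mann-Whitney test could compare a marker by 2-year status. Cox regression is named without restriction, and an analysis plan that is not shown may assign it to the biomarkers.

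Much of this stands. A reader might infer that the protocol explicitly prescribes Spearman for survival times; it does not. What remains is that the objective names four time-to-event outcomes, that correlation is the verb used for it, and that the only method attached to that verb, placed directly after two biomarker tests, cannot use censored data. A comparison by 2-year status needs that status to be known for each patient and does not cover the event times of PFS, DMFS or DSS.

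A reader might also infer that the biomarker analysis will yield many false positives. The documents do not support that: it needs a biomarker related to follow-up length, for example through assay or case-mix drift over accrual, and no such drift is documented.

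**Conclusion.** The point holds as a mismatch between the stated objective and the method named for it. If Spearman is applied to observed OS, PFS, DMFS or DSS times, the correlation is diluted by roughly 20–30% when follow-up runs from 2 to 5 years (HR 1.5 per SD: from about -0.32 to -0.25, or to -0.23 with 10% early drop-out). The power loss is modest in that setting (89% against 96% for Cox at n = 156 without drop-out). Both losses grow if many patients are censored before 2 years.

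The size rests on the assumed hazard ratios, exponential survival and censoring patterns; only the 60% survival, the 10% drop-out and the patient numbers come from the document. The harm is dilution, with type I error near 5%, as long as follow-up length is unrelated to the biomarker.

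A reader might go on to fault the word predictive in a trial without randomisation. The Objectives section makes no treatment-interaction claim, and the word can simply mean predicting response or outcome, so that is not part of this point. The issue concerns a biomarker objective and leaves the primary endpoint and the sample size as they are.

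**What to change.** In Subsequent analyses, state that the association of each biomarker with OS, PFS, DMFS and DSS is estimated by the Cox regression already named there and reported as a hazard ratio with its confidence interval. State that Spearman coefficients are limited to fully observed variables, such as one marker against another or a marker against a QOL score.

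The cost is analysis wording only: no new data, patients or visits. The article describes the study as still ongoing, so the change could be made before the biomarker analysis. If an analysis plan already makes this assignment, a cross-reference is enough.
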